### Randomisation and blinding

People with sub-syndromal symptoms of depression are at greater risk of developing a full-blown depressive episode during the subsequent year than those free of such symptoms [39]. In order to minimise the risk of imbalance, we will stratify the randomisation procedure of women deemed eligible to join the study according to the presence or absence of subsyndromal symptoms of depression, which will be defined by PHQ-9 scores between 5 and 14, inclusive. Participants in each of these two strata will be randomly assigned to the intervention or usual care according to a list of random numbers generated by computer in blocks of 12 or 24. As a consequence of the design of this study, participants and the Health Promotion Officer will not be blind to group allocation, but staff responsible for the administration and coding of the MINI will be blind to it. Both participants and staff will be instructed not to discuss any aspects of the intervention during assessment with the MINI. We are also mindful of the fact that history of past depression is a risk factor for the development of subsequent depressive episodes. Because of the randomisation, history of past depression should not bias the results of the trial. Nonetheless, we will monitor the study for possible imbalances and will adjust the analyses of outcomes, if necessary.

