### Why is the prevalence of depressive symptoms high during the menopausal transition?

The reasons for the increased vulnerability to depression during the MT are not fully understood. Women with past history of depression are nearly five times more likely to have a recurrence of depressive illness during the menopausal transition, whereas women with no history of depression are two to four times more likely to report depressed mood compared with premenopausal women [6, 14, 15]. In some studies, the changing hormonal milieu has been associated with depressive symptoms during the MT [16, 17], but other factors may be as important, such as prolonged hot flushes, weight gain, comorbid diseases, poor social support, changing psychosocial roles, anxiety and perceived loss of control [18–21].

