### Participants

We will use the Australian Electoral Commission roll to obtain a random extraction of 40,000 women aged 45 to 55 years living in the Perth metropolitan area (enrolment to vote is mandatory for all adults in Australia). They will be contacted by post to confirm their perimenopausal status (menopausal transition) and to assess the prevalence of clinically significant symptoms of depression (Patient Health Questionnaire, PHQ-9 score ≥15). They will be asked to return their screening questionnaire alongside the signed consent form, and those with PHQ-9 < 15 will be invited to join the trial. This screening questionnaire will take approximately 30 minutes to complete and will collect the following information:demographics including date and place of birth, age, marital status, number of children, educational attainment, living arrangements;regularity of menstrual cycles to establish menopausal status;history of life-limiting medical illnesses;presence of significant hearing or visual impairment;current and past common medical conditions, including depressive and anxiety disorders;alcohol use, as measured by the Alcohol Use Disorders Identification Test (AUDIT, details below);history of gynaecological surgery and medical procedures (for example, contraceptive implants) that may affect the assignment of menopausal status;prescription and non-prescription medications (including hormone therapy);depressive and anxiety symptoms, as rated by the Hospital Anxiety and Depression Scale (HADS, details below);past history of schizophrenia, schizoaffective, delusional or bipolar disorder; andgeneral practitioner’s (GP) details and permission for the study team to liaise with GP.

For the trial, we will include women who are:aged 45 to 55 years;experiencing no, or sub-threshold depressive symptoms (PHQ-9 < 15);experiencing recent (last 5 years) onset of irregular menstrual cycles (≥7 days difference in length of consecutive cycles) OR ≥2 skipped cycles and at least one interval of amenorrhea of 60 or more days; andamenorrhoeic for <12 months.

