### Sample size

Data from the Australian National Survey suggest that the prevalence of clinically significant depression is 14% around the MT and about 6% immediately before the MT or after the menopause [5]. An effective intervention should decrease the prevalence of depression amongst these women from 14% to 6%, which would represent an absolute risk reduction of 8%. The expected number of women that we will need to treat to prevent one person developing depression is 13. A sample size of 300 women (1:1 allocation) will give the study 80% power to declare such a difference as statistically significant (alpha = 5%). These numbers take into account a loss of 40 women during the course of the study.

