### Statistical methods

Data analysis will be blind to group assignment. We will use descriptive statistics to summarise study measures and will compare their distribution at the baseline assessment for the intervention and control groups using t-tests, Mann-Whitney tests and Pearson’s chi-square statistic. Analyses of outcomes will be intention-to-treat (ITT) and will be ascertained using xtlogit models for binary outcomes (for example, developed a depressive episode during follow up: yes/no. Effect expressed as odds ratio and respective 95% confidence limits) and multilevel mixed-effects linear regression (xtmixed models) to analyse changes in scale scores over time (for example, changes in HADS scores - effect estimate expressed as mean change of score from baseline). We will also use contingency tables to calculate the number needed to treat (NNT) for one person to benefit from the intervention, taking into account the number of participants who may be lost during follow up. The NNT is the reverse of the absolute risk reduction. Alpha will be set at 5% and all statistical tests will be two-tailed. Data from this trial will determine if the intervention causes benefit, harm or neither.

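### Adjustment for past depression hangs on an undefined imbalance check, so the primary model is settled after seeing the data and modest power is given up

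*Protocol article*

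**What the plan says.** Under Randomisation and blinding, the protocol article acknowledges that "history of past depression is a risk factor for the development of subsequent depressive episodes". It argues that randomisation should keep this from biasing the trial, and then adds that "we will monitor the study for possible imbalances and will adjust the analyses of outcomes, if necessary". It does not say what size of imbalance counts, how it is judged, or what the adjusted model would be.

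Randomisation is stratified on a different factor, "according to the presence or absence of subsyndromal symptoms of depression, which will be defined by PHQ-9 scores between 5 and 14, inclusive".

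The Background puts a size on the past-depression effect: "Women with past history of depression are nearly five times more likely to have a recurrence of depressive illness during the menopausal transition". Under Participants, the screening questionnaire collects "current and past common medical conditions, including depressive and anxiety disorders", so the variable is known for every woman before allocation.

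Statistical methods names a Stata xtlogit model with an odds ratio for binary outcomes and mentions no covariates. It also says that the investigators "will compare their distribution at the baseline assessment for the intervention and control groups using t-tests, Mann-Whitney tests" and chi-square statistics. It states that data analysis will be blind to group assignment.

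**The concern.** Whether a baseline variable belongs in the outcome model depends on how strongly it predicts the outcome. Whether the arms happen to differ on it is the wrong trigger, because in a properly randomised trial any such difference is chance. The article already has the relevant information: it regards past depression as prognostic and will hold the data at baseline.

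Two things are at stake. First, with no criterion, two primary analyses are possible, and the choice between them is made with the data in hand. They can disagree on significance. On the logistic scale they also estimate different odds ratios, one marginal and one conditional on past depression. Second, a rule that adjusts only on marked imbalance rarely adjusts, so it forgoes most of the power that planned adjustment would give.

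**Working it through.** **Inputs from the article.** Event rates 14% and 6%; 300 women less 40 lost = 260, or 130 per arm; alpha 5%, two-sided; past depression nearly five-fold.

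**Inputs assumed.** The prevalence of past depression is not given: 20%, 30% and 40% were used, or 35% when the stratum was added. The article does not say whether five-fold is an odds ratio or a risk ratio: odds ratios of 2 to 7 were used. If it is a risk ratio and prevalence is 30%, the risk without past depression is 0.14/(0.7 + 0.3 × 5) = 0.064 and with it 0.318, an odds ratio of 6.9, inside that range. No size is given for the stratum effect: odds ratios of 2, 4 and 6, and a 40% share with PHQ-9 of 5 to 14, were assumed. Each woman has one binary outcome, a simplification of xtlogit.

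**The plan's own figure.** The article says: "A sample size of 300 women (1:1 allocation) will give the study 80% power". With the pooled two-sided formula:

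n per arm = [1.960·√(2 × 0.10 × 0.90) + 0.842·√(0.14 × 0.86 + 0.06 × 0.94)]² / 0.08² = (0.8315 + 0.3539)² / 0.0064 = 220.

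Power at 130 per arm = Φ[(0.08·√130 − 0.8315)/0.4205] = Φ(0.19) = 57.6%. The stated 80% is not reproduced. That is a separate matter, but it sets the starting level here.

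**Past depression alone** (40,000 simulated trials per row, 130 per arm):

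| OR of past depression | Prevalence | Power, never adjusted | Power, adjusted only if imbalance p<0.05 | Power, always adjusted | Adjusted and unadjusted disagree on significance |
|---|---|---|---|---|---|
| 3 | 30% | 56.3% | 56.4% | 57.9% | 5.7% |
| 5 | 20% | 55.9% | 56.1% | 59.4% | 8.4% |
| 5 | 30% | 56.5% | 56.5% | 59.7% | 8.3% |
| 5 | 40% | 56.5% | 56.7% | 59.2% | 7.8% |
| 7 | 30% | 56.6% | 56.7% | 61.0% | 10.1% |

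The gain is about 3 points at OR 5 and about 1 to 4 over OR 2 to 7. An imbalance test at p<0.05 fires in about 5% of trials however prognostic the variable is, so that version of the rule behaves like never adjusting.

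**Change of target.** The marginal odds ratio is (0.06/0.94)/(0.14/0.86) = 0.39. The odds ratio conditional on past depression at OR 5 is about 0.37. The median standard error of the log odds ratio rises from about 0.455 to 0.47 with adjustment. The gain is in power, because the effect moves further from 1.

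**Type I error at OR 5.** It is about 4.5% under a fixed imbalance test and about 6.0% if the better of the two results may be taken (5.3% to 6.4% over OR 2 to 7). In trials with imbalance at p<0.20, it is 6.6–6.7% unadjusted against 4.4–4.6% adjusted.

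**Why the missing criterion matters.** At 30% prevalence and 150 per arm, the chance difference in prevalence has standard deviation √(2 × 0.3 × 0.7/150) = 0.053, so differences up to about 10 points are within the 95% range. A difference of 8 points (0.08/0.053 = 1.5 standard deviations) would not be significant, yet could reasonably be thought to need adjustment. The article does not decide such a case.

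**Adding the randomisation stratum** (16,000 trials per scenario, past-depression OR 4.9):

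| Stratum OR | Unadjusted | Past depression only | Both |
|---|---|---|---|
| 4 | 56.9% | 59.5% | 62.1% |
| 6 | 56.4% | 58.8% | 62.7% |

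The combined gain is 62.1 − 56.9 = 5.2 and 62.7 − 56.4 = 6.3 points. A separate run of 12,000 trials gave 4.8 and 5.7. If both odds ratios are 2, the combined gain is about 2 points at most. Type I error moves from about 4.3% unadjusted to about 5% with both covariates, since stratified randomisation that the analysis ignores makes the test slightly conservative. At matched type I error the combined gain is about 2.5 to 3 points.

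**The case against.** The strongest reply is that a journal article condenses the plan, and covariate lists usually sit in an analysis plan that is not shown. That disposes of any complaint that Statistical methods lists no covariates. It does not dispose of this point, because the article states a rule: adjustment depends on imbalance. A later plan must either inherit that rule or contradict it.

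The steering risk is also limited, since the analysis is blind to group. This makes it hard to choose a model to favour a given arm. It does not fix the model, and a blinded analyst can still see which version is significant.

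Several stronger readings are tempting but not supported:

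- A reader might infer that the baseline significance tests are the trigger for adjustment. The article never links the two. The p<0.05 trigger is an assumption of the simulation.
- A reader might infer that the rule inflates type I error. A fixed imbalance test does not; only free choice of the better result does, and then to about 6%.
- A reader might call past depression the strongest predictor named. The article gives no size for the stratum effect, and the Background's comparator is unclear, so no ranking is possible. Because women with PHQ-9 of 15 or more are excluded and lower symptoms are stratified, the effect within this trial may also be smaller than five-fold.
- A reader might charge the whole 5 to 6 points to the sentence on past depression. About half comes from the stratum, which that sentence does not concern.

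**Conclusion.** The point stands as a recommended change of modest numerical size. The main weakness is that the primary model and its odds ratio are left to an unstated judgement made after seeing the data, for a covariate whose relevance the article already accepts. At an odds ratio of 5, the two candidate analyses disagree on significance in about 8% of trials (3% to 10% over OR 2 to 7).

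The power forgone by not planning adjustment for past depression is about 1 to 4 points. The figure of 5 to 6 points applies only with both covariates and strong assumed effects, and part of it is recovered type I error. All these sizes rest on assumed prevalence, stratum share and stratum effect, and on one outcome per woman. The direction does not depend on those values; the size does.

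**What to change.** Replace the sentence on monitoring imbalances with: *The primary model will include history of depression (yes/no) and the randomisation stratum (PHQ-9 <5 vs 5–14) as covariates, whatever their observed balance.* State that baseline significance tests will not be used to choose covariates.

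The cost is wording only, since both variables are already collected before allocation. Under the planned effect about 130 × (0.14 + 0.06) = 26 events are expected, so the primary model should stop at these two covariates. There are two things to accept. The reported odds ratio becomes conditional on the covariates, with a slightly larger standard error, and should be described as such. The change also does not close the gap to 80%: with both covariates, power at 130 per arm is still only about 62–63% under the strong assumed effects.

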### Statistical methods

Data analysis will be blind to group assignment. We will use descriptive statistics to summarise study measures and will compare their distribution at the baseline assessment for the intervention and control groups using t-tests, Mann-Whitney tests and Pearson’s chi-square statistic. Analyses of outcomes will be intention-to-treat (ITT) and will be ascertained using xtlogit models for binary outcomes (for example, developed a depressive episode during follow up: yes/no. Effect expressed as odds ratio and respective 95% confidence limits) and multilevel mixed-effects linear regression (xtmixed models) to analyse changes in scale scores over time (for example, changes in HADS scores - effect estimate expressed as mean change of score from baseline). We will also use contingency tables to calculate the number needed to treat (NNT) for one person to benefit from the intervention, taking into account the number of participants who may be lost during follow up. The NNT is the reverse of the absolute risk reduction. Alpha will be set at 5% and all statistical tests will be two-tailed. Data from this trial will determine if the intervention causes benefit, harm or neither.

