### Women undergoing the menopausal transition require a targeted health promotion intervention

The MT affects all ageing women with intact ovaries. Marked physiological and psychosocial changes characterise this unique period of a woman’s life, including symptoms such as hot flushes and night sweats, remodelling of body shape, shifting social roles (for example, children moving away from home), and onset of chronic illnesses (such as diabetes and hypertension). All these factors may interact to facilitate the development of depressive symptoms during the MT. As depression and poor lifestyle practices in mid life have been associated with poor health outcomes in older age [11, 27–29], developing health promotion interventions that are relevant to women in the MT seem not only desirable, but a necessity.

In summary, published observational data suggest that women undergoing the MT are at increased risk of clinically significant depressive symptoms and highlight numerous health and behavioural factors that might potentially mediate such increased risk. We have designed a health promotion intervention that seeks to address these risk factors systematically and to enhance behaviours associated with good mental health outcomes. More specifically, this study will aim to address the following:determine the efficacy of a telephone-medicated health promotion intervention, compared with usual care, in decreasing the 12-month incidence of clinically significant symptoms of depression in women undergoing the menopausal transition who do not have clinically significant symptoms of depression or mental disorders at the time of entry into the study,determine the efficacy of a telephone-mediated health promotion intervention in decreasing the 12-month incidence of major depressive episodes in women undergoing the menopausal transition, compared to usual care,measure the effect of a telephone-mediated health promotion intervention in decreasing the severity of depressive symptoms over 12 months compared to usual care,ascertain the prevalence of clinically significant symptoms of depression among community-dwelling Western Australian women undergoing the menopausal transition.

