### Outcomes and study measures

The onset of clinically significant symptoms of depression or of a major depressive episode over 12 months represents the primary endpoint of interest of this trial. We will use the Patient Health Questionnaire (PHQ-9) to establish the presence of clinically significant symptoms of depression. The PHQ-9 is the self-administered depression module of the PRIME-MD diagnostic instrument for common mental disorders. It consists of nine questions about how often the respondent has been bothered by depressive symptoms during the past two weeks, and each item can be scored 0 (not at all), 1 (several days), 2 (a week or more) or 3 (nearly every day). The nine items are as follow: (a) decreased interest or pleasure, (b) low mood, (c) sleep disturbance, (d) lack of energy, (e) disturbed appetite, (f) feelings of failure or guilt, (g) poor concentration, (h) psychomotor disturbance, and (i) suicidal thoughts. The scale has well-established psychometric properties and face-validity, with scores of 15 or greater indicating the presence of clinically significant symptoms of depression that warrant treatment [32]. Endpoints will be collected at 8, 26 and 52 weeks. Another primary endpoint of interest is the onset of a DSM-IV-TR major depressive episode during follow-up, as ascertained by the Mini-Neuropsychiatric Interview (MINI) 8, 26 and 52 weeks after the baseline assessment [33]. The MINI can take between 15 and 45 minutes to complete and it will allow us to investigate the presence of depressive episodes that may have occurred between assessments [34]. Only women who score 15 or more on the PHQ-9 will undergo assessment with the MINI.

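### The panel logit named for binary outcomes does not match the primary endpoint, which is onset counted once per woman over 12 months

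*Protocol article*

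**What the plan says.** The aims at the end of the Background speak of efficacy "in decreasing the 12-month incidence of clinically significant symptoms of depression in women undergoing the menopausal transition". Outcomes and study measures agrees: "The onset of clinically significant symptoms of depression or of a major depressive episode over 12 months represents the primary endpoint". Both describe something that a woman either does or does not reach once within the year.

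The data come from three follow-up visits: "Endpoints will be collected at 8, 26 and 52 weeks". The PHQ-9 asks "how often the respondent has been bothered by depressive symptoms during the past two weeks", so a score at a visit describes current status. The MINI can look back between visits, but that section gives it only to women who score 15 or more on the PHQ-9.

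Statistical methods says that intention-to-treat effects will be estimated "using xtlogit models for binary outcomes (for example, developed a depressive episode during follow up: yes/no", with "Effect expressed as odds ratio and respective 95% confidence limits". It adds "We will also use contingency tables to calculate the number needed to treat (NNT) for one person to benefit from the intervention". It does not name the form of xtlogit (random-effects, fixed-effects or population-averaged), the number of rows per woman, or whether a woman leaves the risk set after her first onset.

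**The concern.** The model and its example outcome stand in the same sentence and do not fit together. A panel logit needs several rows per person, whereas ever having developed an episode during follow-up supplies one. To get several rows, the analyst would have to change the outcome to something recorded at each visit. The natural candidate is being at or above the PHQ-9 threshold at that visit, and that is a different quantity from onset.

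This matters here because the intervention could plausibly shorten episodes without preventing them. The Intervention section includes better management of depressive symptoms and active monitoring among its aims, and session five covers recognising onset and seeking help. On visit status, a woman who stays depressed counts up to three times and a woman who recovers counts once. Shorter episodes could then look like prevention, in the only effect model that the article names for its primary endpoint.

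**Working it through.** **Inputs.** From Sample size: 14% against 6%, 300 women, loss of 40, hence (300 − 40)/2 = 130 per arm. From Outcomes and study measures: three follow-up visits and a two-week recall. Assumed, because the article gives nothing: event counts of 18 and 8 (close to 14% and 6% of 130), onset equally likely at each visit, the persistence values below, and no recurrence.

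**The plan's own figures.** 0.14 − 0.06 = 0.08 and 1/0.08 = 12.5, which rounds up to the stated number needed to treat of 13. The matching once-per-woman odds ratio is (0.06/0.94)/(0.14/0.86) = 0.39.

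**One row per woman.** With arm as the only covariate, the data determine two marginal risks, while the random-intercept model has three parameters (intercept, arm effect, between-woman SD). For any SD, the other two can be chosen to reproduce 18/130 and 8/130 exactly. Numerical integration over the random intercept gives:

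| Between-woman SD | Log-likelihood | Odds ratio for arm |
|---|---|---|
| 0 | −82.334 | 0.41 |
| 1 | −82.334 | 0.37 |
| 2 | −82.334 | 0.29 |
| 3 | −82.334 | 0.20 |
| 5 | −82.334 | 0.09 |

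The likelihood is flat, so the data cannot choose among these odds ratios. The fixed-effects form also fails, because one row per woman contains no within-woman variation.

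**Three visit rows per woman.** Let a case at one visit still be a case at the next with probability p. Onset at the first, second or third visit gives on average 1 + p + p², 1 + p or 1 positive visits. Hence visit prevalence = onset risk × (3 + 2p + p²)/9.

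Equal onset of 14%, shorter episodes under intervention:
- Control, p = 0.7: 0.14 × 4.89/9 = 0.0761.
- Intervention, p = 0.2: 0.14 × 3.44/9 = 0.0535.
- Visit-level odds ratio: (0.0535/0.9465)/(0.0761/0.9239) = 0.69. The onset odds ratio is 1.00.

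The same formula gives the population-averaged column below. The random-intercept column comes from fitting that model, without visit effects, to 100,000 simulated women per arm. The same simulations gave population-averaged values of 0.68, 0.42 and 0.60.

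| Onset, control vs intervention | Persistence, control vs intervention | Onset OR | Visit OR, population-averaged | Visit OR, random intercept |
|---|---|---|---|---|
| 14% vs 14% | 0.7 vs 0.2 | 1.00 | 0.69 | 0.71 |
| 14% vs 6% | 0.5 vs 0.5 | 0.39 | 0.41 | 0.26 |
| 14% vs 6% | 0.2 vs 0.7 | 0.39 | 0.60 | 0.40 |

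When persistence is equal, the population-averaged odds ratio barely moves from the onset value. When it differs, the visit-level result can suggest benefit where there is no prevention (first row), or the population-averaged value can understate real prevention (third row). The 0.26 in the second row is not a bias: a random-intercept odds ratio is conditional on the woman and lies further from 1 than the marginal one.

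**The case against.** The strongest defence is that the article consistently describes onset, and that only the command name is awkward. Two uses of xtlogit would respect that description. In its population-averaged form with one row per woman it reduces to ordinary logistic regression. With each woman's visit rows kept only until first onset it gives a discrete-time onset odds ratio. An article may leave form and row layout to the analysis plan, and the sentence covers binary outcomes in general, including repeated ones such as psychotropic medication use, for which a panel logit is reasonable.

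Much of this stands. A reader might infer that xtlogit must either fail or estimate prevalence. The document does not support that, because neither of these two uses is ruled out. A reader might also build a more dramatic example: equal 14% onset, every control episode present at all three visits and every intervention episode at just one. Visit prevalence is then 14% against 14/3 = 4.67%, an odds ratio of 0.30 against a true 1.0. Nothing in the article suggests so extreme a pattern. Finally, a reader might fault the contingency-table number needed to treat. It is not an error: it counts each woman once and sits on the same absolute scale as the design target.

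The defence does not remove the mismatch itself. The article does not omit the model; it names one and illustrates it with an outcome that the usual form of that model cannot handle. The MINI look-back does not settle the matter either, since it is reserved for women already at or above the PHQ-9 threshold at that visit. The contingency tables are offered for the number needed to treat, not as the intention-to-treat effect estimate.

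**Conclusion.** The point holds as a mismatch between the stated model and the stated outcome. With one row per woman the random-effects form is not identified; this follows from the model structure and does not depend on the assumed counts. With visit-status rows the target becomes visit-level odds. How far that departs from onset depends on whether persistence differs between arms, on which the article gives no information: almost nothing on the population-averaged scale at 0.5 in both arms, and about 0.7 against 1.0 at 0.7 versus 0.2. These values are illustrations, not predictions.

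It does not follow that the trial would be analysed wrongly, since an unseen analysis plan may specify a suitable variant. As published, though, one sentence allows materially different primary odds ratios from the same data.

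**What to change.** For the primary endpoint, replace xtlogit with a model of first onset by 12 months, adjusted for the PHQ-9 randomisation stratum. Either of these would do:

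- logistic regression with one row per woman; or
- a discrete-time model on the intervals 0–8, 8–26 and 26–52 weeks, with terms for arm, interval and stratum, each woman leaving the risk set at first onset or last visit. The 12-month risk is 1 − (1 − h₁)(1 − h₂)(1 − h₃), where h is the fitted interval risk. This option uses the partial follow-up of women who drop out.

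Report the 12-month risk difference with its 95% confidence interval beside the odds ratio. The planned number needed to treat can stay. Keep xtlogit for secondary binary outcomes measured repeatedly, or for a secondary analysis of visit prevalence, and state its form there.

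The cost is a few lines of wording and code, with no new data collection. The one small drawback is that the headline effect measure may change.
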